### Interventions

#### Provider education

Between February and April 2008, we provided all participants with the current JNC 7 hypertension guidelines during live educational webinars presented by a cardiologist and an internist. At the sessions, participants learned their study arm assignment. Participants in the intervention arms received information about the magnitude and criteria for the incentives.

#### Audit and feedback

All participants (including the control group) received an audit and feedback report via a secure, password-protected study website following the end of each of five data collection periods, approximately four months apart. Reports were designed to contain features, which in previous research had improved the effectiveness of feedback in healthcare settings [20,21]. Reports included data reflecting individual and group scores, earnings for the study period, total earnings to date, and future performance goals. Each time we posted the feedback report for a particular period to the website, we emailed study participants to announce its availability. Figure 2 shows the layout of the audit and feedback report for a physician participant in the combined incentive arm.

**Figure 2 F2:**
[figure not shown]
**Feedback report #3 for a physician participant in the individual and group incentives study arm**. BP = blood pressure.

#### Financial incentives

The financial incentive intervention phase of the study started in April 2008 and consisted of disbursements of incentive payments earned over each of five performance periods. For each performance period, trained chart abstractors extracted relevant data from the VA electronic medical records of 40 randomly selected patients in each physician's panel who met eligibility criteria. Only those patients with hypertension who had a face-to-face healthcare encounter where hypertension could be addressed during the performance interval were eligible for inclusion in the sampling frame. For the first performance period, we examined a four-month period prior to the start of the incentive intervention phase to assess participants' baseline performance. We anchored performance periods two to five from the start of the incentive intervention phase. Incentive payments arrived in participants' VA paychecks approximately every four months and typically followed the posting of the feedback report for that performance period. After each data collection period, we notified participants via e-mail the date of the paycheck in which the payment was to appear.

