**Methods/design:**

This randomized controlled trial tests whether explicit financial incentives promote the translation of guideline-recommended care for hypertension into clinical practice and improve blood pressure (BP) control in the primary care setting. Using constrained randomization, we assigned 12 Veterans Affairs hospital outpatient clinics to four study arms: physician-level incentive; group-level incentive; combination of physician and group incentives; and no incentives (control). All participants at the hospital (cluster) were assigned to the same study arm. We enrolled 83 full-time primary care physicians and 42 non-physician personnel. The intervention consisted of an educational session about guideline-recommended care for hypertension, five audit and feedback reports, and five disbursements of incentive payments. Incentive payments rewarded participants for chart-documented use of guideline-recommended antihypertensive medications, BP control, and appropriate responses to uncontrolled BP during a prior four-month performance period over the 20-month intervention. To identify potential unintended consequences of the incentives, the study team interviewed study participants, as well as non-participant primary care personnel and leadership at study sites. Chart reviews included data collection on quality measures not related to hypertension. To evaluate the persistence of the effect of the incentives, the study design includes a washout period.

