### Data analysis

The unit of analysis will be the physician. We will perform a repeated measures longitudinal analysis using mixed models to evaluate the effect of the intervention. We will evaluate three different predictors for each outcome: each incentive arm versus the control arm; individual-level incentive arms versus arms with no individual incentives; and group-level incentive arms versus arms with no group incentives. Models will be developed independently for each outcome. First, using scientifically relevant covariates selected *a priori*, we will construct a maximal model for each outcome as described by Cheng *et al*. [22]. The maximal model provides the flexibility to evaluate both the covariance structure and the list of covariates for inclusion in the final model. The relationship between each continuous covariate and the outcome will be explored to assess the need for covariate transformations. We also will determine whether any site-to-site variation exists and include the facility (cluster) as a random effect as necessary. We then will perform backward elimination to delete variables of no value, arriving at our final model.

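### Performance period 1 is described both as pre-intervention baseline and as one of five incentive periods, and the analysis section neither fixes its role nor protects a baseline term from deletion

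*Protocol article*

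**What the plan says.** All references are to the protocol article.

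- **Financial incentives**, on timing: "For the first performance period, we examined a four-month period prior to the start of the incentive intervention phase". The purpose given is "to assess participants' baseline performance". The later periods start with the intervention: "We anchored performance periods two to five from the start of the incentive intervention phase".
- **Financial incentives**, on payment: the incentive phase, begun in April 2008, "consisted of disbursements of incentive payments earned over each of five performance periods". Period 1 is thus one of the five paid periods.
- **Abstract, Methods/design**: performance was rewarded "during a prior four-month performance period over the 20-month intervention".
- **Data analysis**: "We will perform a repeated measures longitudinal analysis using mixed models to evaluate the effect of the intervention". The predictors to be evaluated are "each incentive arm versus the control arm; individual-level incentive arms versus arms with no individual incentives", and the same comparison for group incentives. Covariates are chosen a priori but not listed, and backward elimination leads to the final model. The facility random effect enters only if needed.
- **Provider education**: sessions ran from February to April 2008. "At the sessions, participants learned their study arm assignment", and the incentive arms were told the size of the payments and the criteria.

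**The concern.** A period that ended before the incentives began cannot show an incentive effect. It is useful as a baseline, because with three hospitals per arm much of the noise is hospital-to-hospital difference, and a baseline can remove the stable part of it. The article gives period 1 both roles, and the analysis section does not choose between them. Two things are at stake. One is the estimand: an arm effect averaged over five periods is not the effect of the incentives while they were in force. The other is precision: a baseline that has already been abstracted could be left out of the model or eliminated from it. A lesser question is whether the baseline window ends before participants knew their arm.

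**Working it through.** **1. Length of exposure.** Five periods × 4 months = 20 months, which matches the abstract. Periods 2 to 5 give 4 × 4 = 16 months. The stated 20 months is reached by counting the pre-intervention period (or five payments about four months apart), not by time under incentive.

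**2. Dilution under one common arm effect.** With equal weight on each period (balanced data, compound symmetry) and a mean effect D over periods 2 to 5, the five-period effect is (0 + 4D)/5 = 0.8D.

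- The detectable differences in Power and sample size, 17 and 15 points, would appear as 13.6 and 12.0.
- The Table 3 footnote projects physician-arm gains of 0.05 (process) and 0.03 (BP control) per period. Medication: (5+10+15+20)/4 = 12.5 points over periods 2 to 5, and (0+5+10+15+20)/5 = 10 over all five. BP control: 7.5 and 6.
- With an arm-by-period contrast the dilution is 0%, even if period 1 stays in the response vector.

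**3. What baseline adjustment could buy.** The detectable differences are not used as a power benchmark, because no single standard variant tried reproduces 80% for both (three v three hospitals, alpha 0.05, df 4 gives 54% and 58%). Only the implied SDs and the stated ICCs are used.

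- SD: 17/1.59 = 10.7 points; 15/1.30 = 11.5 points. Total variance: 0.01143 and 0.01331.
- Hospital variance (ICC 0.39, 0.14): 0.00446 and 0.00186.
- Binomial error on 40 charts: 0.006 (assumed; for example 0.6 × 0.4/40).
- Physician variance, the remainder: 0.00097 and 0.00545.
- Further assumptions: 7 physicians per site, physician effects fully stable across periods, no change in controls, Table 3 gains, two-sided alpha 0.05, df 8 (7 with baseline). The hospital correlation between periods, ρ, is not in the document and is varied.

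Power comes from the non-central t with effect/√(2v/3), where v is the variance of a site's mean. Worked example, medication, ρ = 1:

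- Five periods: v = 0.00446 + 0.00097/7 + 0.006/35 = 0.00477; 0.10/0.0564 = 1.77; power 35%.
- Periods 2 to 5 adjusted: v = 0.00481 − 0.00460²/0.00546 = 0.00094; 0.125/0.0250 = 5.0; power 99%.

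| Measure | ρ | Five periods, common effect | Periods 2–5, unadjusted | Periods 2–5, adjusted for period 1 |
|---|---|---|---|---|
| Medication | 1.0 | 35% | 49% | 99% |
| Medication | 0.5 | 50% | 67% | 81% |
| Medication | 0.3 | 62% | 77% | 82% |
| BP control | 1.0 | 23% | 33% | 77% |
| BP control | 0.5 | 30% | 41% | 59% |
| BP control | 0.3 | 34% | 46% | 57% |

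**4. Sensitivity.** With df 4 (3 with baseline) and ρ = 0.3, medication power is 64% unadjusted and 62% adjusted, so adjustment gains nothing. Power and sample size calls for a multiplicity correction. At alpha 0.05/3 (an assumed form), the adjusted powers for ρ from 0.5 to 1.0 fall to 60–94% (medication) and 36–54% (BP control).

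**5. Disclosure.** If period 1 is the four months immediately before April 2008, it overlaps the February–April sessions. The text says only that the period came before the start, and the timeline figure is not available here.

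**The case against.** A reader might infer that the plan fits all five periods as outcomes with no baseline adjustment, so that the effect is biased towards zero. The document does not say so. Data analysis names the predictors of interest, not the full model. It does not say which periods are responses, and the unlisted a priori covariates may include baseline performance. An article commonly leaves covariate lists and time coding to the full protocol or analysis plan. Calling period 1 a baseline suggests that the authors meant to use it as one. A longitudinal model with period 1 as a response is also a valid adjustment when the effect is an arm-by-period contrast. All of this stands, and it limits the point to what the text leaves open.

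A reader might also take 81–99% and 59–77% as the power that adjustment would deliver. Set against 35–50% and 23–30%, those ranges compare the least favourable reading with the best remedy, for ρ from 0.5 to 1.0 only. At ρ = 0.5, more than half of the medication gain (50% to 67%) comes from excluding period 1, and the rest (67% to 81%) from the covariate. The projected gains were made to estimate payouts, and controls also received education and feedback, so zero change in controls is generous.

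A contaminated baseline is likewise only possible, since the dates are not given.

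The objection does not remove the two roles given to period 1, the 20 against 16 months, or the lack of protection for a baseline term under backward elimination. These are in the text.

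**Conclusion.** The point holds as an inconsistency and an open analysis choice, not as a demonstrated bias. Period 1 is called baseline and also counted as an incentive period, and stated exposure is four months longer than periods 2 to 5 allow. The analysis section leaves room for a model in which the arm effect is diluted by 20%; the dilution is zero under an arm-by-period contrast or an analysis of periods 2 to 5. The gain in precision from baseline adjustment is large if hospital differences are stable over time, and negligible at a correlation of about 0.3 with few degrees of freedom. The power figures above should be read only with their assumptions. Settling the choice in advance is worthwhile because the trial has 12 clusters and the remedy is nearly free.

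**What to change.** 1. State that period 1 is the baseline and that incentive exposure comprises four performance periods (16 months). Reconcile the abstract and Financial incentives with this, keeping the number of payments separate from the length of exposure.
2. In Data analysis, define the arm effect as the arm difference over periods 2 to 5, adjusted for period-1 performance. Alternatively, keep period 1 as a response, constrain the arms to be equal there, and estimate the arm-by-period contrast.
3. Exempt the baseline and period terms from backward elimination.
4. Give the period-1 dates relative to the February–April 2008 sessions. If they overlap, add a sensitivity analysis in which the baseline uses only encounters before each site's session.

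The cost is wording, plus at most one site-level degree of freedom. Period-1 data are already collected. The sensitivity analysis needs encounter and session dates, and would rest on fewer charts per physician.

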#### Study outcomes

We rewarded participants for delivering guideline-concordant care for management of hypertension. Incentive earnings for each four-month performance period were based on the proportion of the physician's sampled patients meeting either or both performance measures: receiving guideline-recommended antihypertensive medications; and achieving the guideline-recommended BP threshold OR having an appropriate response to uncontrolled BP (Figure 3). According to the guideline in place at the time of the study, thiazide diuretics should be used either alone or in combination with other classes of medications to control BP in most patients with uncomplicated hypertension. In patients with compelling indications for the use of other antihypertensive drug classes (*e.g*., diabetes mellitus or renal disease), medications appropriate for those high-risk conditions should be used as initial therapy for controlling BP [2]. JNC 7 guidelines recommend treating BP to a goal of < 140/90 mm Hg in most patients. In those with hypertension and co-existing diabetes mellitus and/or renal disease, the goal was < 130/80 mm Hg. Examples of appropriate responses to uncontrolled BP included increasing the dosage of a guideline-recommended antihypertensive medication or recommending a lifestyle modification, such as the Dietary Approaches to Stop Hypertension (DASH) eating plan to a patient with Stage 1 hypertension.

**Figure 3 F3:**
[figure not shown]
**Study outcomes assessed to determine incentive payment**. JNC 7 = Seventh Report of the Joint National Committee on Prevention, Detection, Evaluation, and Treatment of High Blood Pressure. *Blood pressure control for patients without co-existing diabetes defined as < 140/90 mm Hg; with co-existing diabetes < 130/80 mm Hg. †Defined as either adding new or increasing current antihypertensive medication, prescribing lifestyle modifications, or rechecking the patient's blood pressure within six weeks to determine if blood pressure controlled; if not controlled, responding with at least one of above actions.

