To avoid the problems associated with the exclusive use of process-of-care or outcome measures described above and to dampen the gaming incentive, both a process-of-care measure (use of guideline-recommended medications in patients who have no other compelling indications) and an intermediate outcome measure (achievement of the JNC 7 BP goal) will be used. This approach may avoid the pitfalls of process-of-care measures alone that can encourage gaming, while avoiding the disadvantage of basing incentives solely on outcomes that may be relatively rare or difficult to achieve and somewhat beyond the control of the provider. Thus, a combined approach potentially capitalizes upon the advantages and complementary nature of both types of quality-of-care measures [9]. The design of our trial reflects the following logic: other things being equal, process-based incentives will create stronger incentives for improvement in process (which the physician can directly control); similarly, process-based incentives may also produce better outcomes (assuming that the processes being incentivized improve outcomes). We believe that combining outcome-based with process-based incentives has the potential to produce even greater quality improvement than process measures alone [17].

A third design question is whether the incentive payments should be distributed according to relative performance (*i.e*., the participant's percentile ranking compared to peers) or absolute performance (*i.e*., strictly according to performance relative to the same standard)? The former approach may be problematic because participants cannot directly control the behavior or outcomes of others on whom a relative comparison is based. The latter approach rewards behavior that the individual or group can directly control [10,13]. Therefore, we designed our incentives to reward participants each time they provided guideline-recommended medications and/or their patient met the guideline-recommended BP threshold or, in the absence of controlled BP, the participant appropriately responded to uncontrolled BP [17].

In this article, we describe the methods used to assess the effects of physician- and group-level financial incentives on processes and outcomes of care for outpatients with hypertension.

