We provide power calculations for the process and outcome measures. We calculated effect sizes for various values of the difference in percentage use of appropriate medication and BP control we could detect between the study arms with 80% power using a two-sided t-test with 95% significance. Greater increases in power result from increasing the number of clusters than by increasing the number of cases within clusters [18]. However, it is much more difficult and costly to recruit more hospitals. We chose to use three hospitals per study arm with five physicians per hospital and 40 patient charts per physician. We determined that we could detect a difference of 17 percentage points between the mean proportions of appropriate medications in the arms, for an effect size of 1.59. Similarly, for BP control, we determined we could detect a difference of 15 percentage points between the mean proportions in the study arms for an effect size of 1.30.

We adjusted the sample size to account for anticipated physician participant attrition. Using VA physician workforce planning data, we estimated 5.8% would leave VA employment during the study. We adjusted our initial sample size, five physicians per site, to seven per site to account for attrition using the formula proposed by Lachin [19], defined as 1/(1-R)^2 ^where R is the drop-out rate.

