#### Incentive payment structure

The five participating VA Networks' contributions to the incentive fund totalled $250,000. Based on this amount, we then simulated study results using pilot data and estimated rates of improvement to determine the greatest per-outcome incentive that we could provide per physician. The results indicated a per-patient maximum amount of $18.20, one-half from use of guideline-recommended medications and one-half from either BP control or appropriate response to uncontrolled BP.

Table 3 describes the intervention components and estimated incentive payouts for the study arms. For the physician-level incentive arm, each physician's reward reflected the number of successful outcomes achieved among the 40 randomly chosen patients. The group incentive earnings were based on the aggregated performance of the physicians. We allowed participants at the six group sites to choose how to allocate the group earnings (*e.g*., divide earnings among themselves as personal income or use them to provide patient education materials or other supplies for the clinic). Each group chose to divide the earnings evenly amongst themselves. For the combined incentive arm, the physicians received a payment that included their individual performance earnings as well as their share of the group's aggregated performance reward. Non-physician participants received their share of the group's aggregated performance reward.

**Table 3 T3:** Intervention components and incentive payouts

	Intervention components			Participants				Total estimated* incentive over entire study period	
				
Study Arm	Audit/ feedback report	Individual physician incentive	Group incentive	Physicians	Non- physicians	Performance evaluated	Per outcome per patient incentive award	Individual Physician	Group†
Physician incentive	•	•		•		Physician	$9.10	$2681	N/A

Group incentive	•		•	•	•	Physician	$9.10	N/A	$17206

Physician and group incentives	•	•	•	•	•	Physician	$9.10	$2696	$18872

No incentives (control)	•			•		Physician	$9.10	N/A	N/A

*Estimates based on outcome rates from pilot study and projected improvement rates per period as follows: individual arm - 0.05 for process measures (guideline-recommendation medication and appropriate response) and 0.03 for blood pressure control; group arm - 0.02 for process measures and 0.01 for blood pressure control; combined arm - 0.06 for process measures and 0.04 for blood pressure control.

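### The Figure 3 footnote sets the BP-control threshold by diabetes alone, while the Study outcomes text also puts renal disease in the < 130/80 group

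*Protocol article*

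**What the plan says.** Design of incentives ties the outcome measure to the guideline: "an intermediate outcome measure (achievement of the JNC 7 BP goal) will be used". It gives no numbers there.

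Study outcomes makes the second paid measure "achieving the guideline-recommended BP threshold OR having an appropriate response to uncontrolled BP" and then states the threshold. It is below 140/90 mm Hg for most patients, with this exception: "In those with hypertension and co-existing diabetes mellitus and/or renal disease, the goal was < 130/80 mm Hg". The same paragraph names renal disease beside diabetes as an example of a condition that changes the recommended drugs: "diabetes mellitus or renal disease), medications appropriate for those high-risk conditions should be used as initial therapy for controlling BP".

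The Figure 3 footnote, under a caption about the outcomes that determine payment, gives the definition of control: "Blood pressure control for patients without co-existing diabetes defined as < 140/90 mm Hg; with co-existing diabetes < 130/80 mm Hg". Renal disease is not mentioned. A second note lets a BP recheck within six weeks count as an appropriate response, the purpose being "to determine if blood pressure controlled; if not controlled, responding with at least one of above actions".

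Power and sample size treats BP control as a powered measure: "for BP control, we determined we could detect a difference of 15 percentage points between the mean proportions in the study arms". Incentive payment structure splits the $18.20 per-patient maximum in two, with "one-half from either BP control or appropriate response to uncontrolled BP".

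**The concern.** The footnote's two classes, with and without diabetes, cover every patient. A patient with renal disease but no diabetes therefore falls under 140/90, although the text sets that patient's goal at 130/80. No other part of the article reconciles the two, and the footnote is the only place that says how BP control is defined.

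BP control is one of the two powered measures, and control or an appropriate response is one of the two paid measures. If the footnote governed, the reported control level would be too high against the stated JNC 7 goal. In the affected patients, a further fall in BP from 135/85 to below 130/80 would earn no credit.

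**Working it through.** **Step 1. Compare the two rules by type of patient.** The article states no figure that could be reproduced here, so the first check is a comparison of cases.

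| Patient | Study outcomes text | Figure 3 footnote | Agree? |
|---|---|---|---|
| Diabetes, with or without renal disease | < 130/80 | < 130/80 | yes |
| Neither condition | < 140/90 | < 140/90 | yes |
| Renal disease, no diabetes | < 130/80 | < 140/90 | no |

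In the last row the rules give different results only when BP is below 140/90 but not below 130/80. At 135/85, the text says uncontrolled and the footnote says controlled, with no response required. Below 130/80 both say controlled. Not below 140/90 both say uncontrolled.

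**Step 2. The recheck.** The threshold is used again in the response rule. Take the same type of patient at 145/92, rechecked within six weeks at 135/85. Under the footnote the recheck is enough. Under the text the patient is still uncontrolled and one of the listed actions is needed.

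**Step 3. Size, if the footnote was the scoring rule.** The article does not give the number of affected patients, so both shares below are assumptions.

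- p = share of sampled patients with renal disease and no diabetes, assumed 0.05 to 0.15.
- q = share of those with BP between the two goals, assumed 0.20 to 0.40.
- From the article: 40 charts per physician per period, 83 physicians, $9.10 per outcome per patient, five periods, and $2681 as the estimated individual total in the physician-incentive arm (Table 3).
- Affected share: s = p × q.
- Charts per period: 40 × s per physician, and 83 × 40 × s = 3,320 × s overall, taking a full sample for every physician.
- Individual payment per physician per period: 40 × s × 9.10 × (1 − r), where r is the share of affected patients who had a qualifying response anyway. The article does not give r, which can lie anywhere from 0 to 1.

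| | Low | Middle | High |
|---|---|---|---|
| p × q | 0.05 × 0.20 | 0.10 × 0.30 | 0.15 × 0.40 |
| s, the rise in control level (points) | 1.0 | 3.0 | 6.0 |
| Charts per physician, of 40 | 0.4 | 1.2 | 2.4 |
| Charts overall, of 3,320 | 33 | 100 | 199 |
| Payment per period, r = 0 | $3.64 | $10.92 | $21.84 |
| Payment over five periods, r = 0 | $18.20 | $54.60 | $109.20 |
| Share of $2681 | 0.7% | 2.0% | 4.1% |

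At r = 1 the payment effect is $0. The recheck route in Step 2 adds an amount that the article gives no means of estimating.

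**Step 4. If the footnote is shorthand** and charts were scored by the goal in the text, s has no effect and every entry above is zero.

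These are shifts in the level of control. They cannot be set against the detectable difference of 15 points, which is a difference between arms.

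**The case against.** The strongest reply is that the footnote may be shorthand. It annotates a figure that is not reproduced in the text at hand. The legend expands the abbreviation JNC 7, which the caption and notes do not otherwise use, so the figure itself may name the JNC 7 goal. Design of incentives and Study outcomes both tie the measure to the guideline, and Data collection lists renal conditions among the abstracted items. All of this fits renal status having been used in scoring. The abstraction tool that would settle it is not shown. This stands as a limit: the article supports a conflict between two descriptions and does not establish how charts were scored. The conflict itself remains, because shorthand that puts non-diabetic renal patients in the wrong class still needs correcting.

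A second reply concerns the remedy. Incentive-arm participants were told the criteria at the outset, and the final feedback reports were posted in April 2010. If the footnote rule was used, replacing it afterwards would judge physicians on a threshold they were not paid for. Response data may also be absent for patients first scored as controlled. Both objections stand, so the second definition should be added beside the paid one and should not replace it.

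It can also be said that drug choice and BP target are separate questions. That is fair. The mention of renal disease under the medication measure shows only that the authors had the condition in view.

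A reader might go further and infer that charts were mis-scored or that the comparison of arms is biased. The article supports neither. It does not say which rule was used, and nothing in it suggests that the rule differed by arm or period.

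**Conclusion.** The point holds as a contradiction in the definition of a powered and paid outcome, confined to patients with renal disease, no diabetes, and BP below 140/90 but not below 130/80. That conflict is certain from the wording. Its effect on the data is not known: zero if the text's goal was applied, and 1.0 to 6.0 points on the control level if the footnote was applied and the assumed shares are right. The effect on individual payment is small in either case. No bias between arms is shown. It should be corrected because the article otherwise leaves the meaning of controlled BP open for these patients.

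**What to change.** 1. Correct the Figure 3 footnote so that the threshold below 130/80 applies to patients with diabetes, renal disease or both, at the first BP and at the six-week recheck.
2. State which rule governed scoring and payment. If it was the rule in the text, nothing more is needed.
3. If it was the footnote rule, also score BP control by the text's goal in every period from baseline to post-washout. Report results under both definitions, identify the paid one, and leave past payments unchanged.
4. Re-score the combined control-or-response measure only where response data were recorded for the reclassified patients.

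The cost is a little extra programming. Scoring BP control itself needs no new data, because Data collection lists renal conditions and vital signs among the abstracted items. Under the stricter goal the reported control level will be slightly lower, and it may not match the feedback reports already issued.
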